**Notes \* Each blood sample approximately 5-8mls**

The antigens listed shall be given as: DTPa-HepB-Hib-IPV-PRP-T (GlaxoSmithKline), Each vaccine antigen dose number is signified by subscript numbers. E.g. D2T2Pa3 signifies the second vaccination for diphtheria and tetanus toxoids and the third vaccination for the acellular pertussis antigens.

## **8.2 Medication(s)/treatment(s) permitted (including rescue medication) and not permitted before and/or during the trial.**

Any medication is permitted based on clinical indication including those specified in Section 6.3.1.

## **8.3 Clinical and Laboratory Procedures**

### *8.3.1 Clinical Procedures*

The following clinical procedures will be conducted during this study:

- A review of the participant's medical history, including demographics, and concomitant medication
- A brief medical evaluation and other physical examination if clinically indicated.
- Measurement of the participant's axillary temperature.
- A review of the participant's eligibility according to the Inclusion / Exclusion criteria.
- A 5mL blood sample will be collected at visit 1 from the mother and infant blood will be collected at visit 2, 3, 5 and 6 for the determination of antibody titres. The timing and

frequency of the above procedures are described in the Schedule of Assessments (Table 2: Pages 22).

- Participants will be observed for 30 minutes post dPa vaccine at visit 1 and for 15 minutes following vaccinations at visits 2, 4 and 5

### 8.3.2 Blood Samples for Immunogenicity Analysis

Five blood samples will be collected throughout the study. The day of collection and the volume of blood to be collected is summarised below (Table 3).

Table 3: Blood Collection intervals and volume

| Visit Number (Day)                |                | Volume (ml) |
|-----------------------------------|----------------|-------------|
| Visit 1 (up to day 5)             | Maternal blood | 5           |
| Visit 2 (Day 42-56)               | Infant blood   | 5           |
| Visit 3 (28-35 days from Visit 2) | Infant blood   | 5           |
| Visit 5 (Day 176-211)             | Infant blood   | 5           |
| Visit 6 (60-74 days from Visit 5) | Infant blood   | 5           |

## 9 Procedures for monitoring subject compliance.

To ensure that participants receive the correct doses of the vaccines, the study staff must confirm and record the dose volume, batch number and date of administration in the relevant source documentation and then administer the vaccine.

## 10 Adverse Events

The Investigator at each centre is responsible for ensuring that all AEs and other clinically significant findings are documented and accurately reported. All study staff must understand the requirements and responsibilities related to safety reporting that are outlined below.

### 10.1 Definitions

#### 10.1.1 Adverse Event (AE)

As per the International Conference on Harmonisation (ICH), an AE is any untoward medical occurrence in a patient or clinical investigation subject administered a pharmaceutical product and which does not necessarily have a causal relationship with this treatment. An AE can, therefore, be any unfavourable and unintended sign (e.g., an abnormal laboratory finding), symptom, or disease temporally associated with the use of a medicinal (investigational) product, whether or not considered related to the medicinal (investigational) product. All AEs must be recorded in the appropriate section of the source document.

#### Adverse events include:

- Exacerbation (i.e., an increase in the frequency or severity) of a pre-existing condition. Illness present before study entry should be recorded in the medical history section of the source document and only be reported as an AE if there is an increase in the frequency or severity of the condition during the study.
- Intercurrent illnesses with an onset after administration of any one of the study vaccine

a. Solicited Adverse Event

Solicited AEs are those events specifically sought for and recorded by patients in the 7-day diary card.

A solicited AE Diary that will be issued after each vaccination. The diary will constitute source data for this study.

Solicited local AEs that will be collected during this study include: injection site pain, erythema and induration / swelling.

Solicited systemic AEs that will be collected during this study include:

Fever  $\geq 37.5^{\circ}\text{C}$ , reaction such as, drowsiness, periodically more irritable than usual but with normal activity, prolonged crying and refusal to play, prolonged crying and inability to be comforted, anorexia (poor appetite), vomiting judged to be greater than a posset, redness and swelling at the vaccination site each measured in mm, pain scored as none, minor light reaction to touch, crying or protesting to touch, or crying when the leg is moved.

b. Unsolicited Adverse Event

Unsolicited AEs include AEs other than those specifically solicited. Unsolicited AEs will be recorded by the parents/guardians in the Unsolicited AE Diary Card which is issued after each vaccination. The diary will constitute source data for this study. All other medically attended visits between study visits up to visit 6 (8 months old) will be collected

10.1.2 *Serious Adverse Event (SAE)*

A serious adverse event (SAE) is defined as any adverse event that:

- **Is fatal:** The event must be the cause of death for the SAE to meet the serious criteria of “fatal”. (*Note: death is an outcome, not an event*)
- **Is life-threatening:** The term “life-threatening” refers to an event in which the participant was at risk of death at the time of the event; it does not refer to an event, which hypothetically might have caused death if it were more severe.
- **Requires in-patient hospitalisation or prolongation of existing hospitalisation.**
- **Results in persistent or significant disability / incapacity**
- **Is a congenital anomaly / birth defect**
- **Is medically significant according to the investigator’s judgement:** Medical and scientific judgement should be exercised when deciding whether an event is serious. Important medical events that may not be immediately life-threatening or result in death or hospitalisation, but may jeopardise the participant or may require intervention to prevent one of the other outcomes listed in the definition above, may be defined as serious.

Note, at least one of the above criteria must be ticked on the SAE page of the source document.

Please note the following may also constitute reporting of an SAE:

- Any SAE (including medically significant events and AESIs), whether or not related to one of the study vaccines, and occurring from Day 0 up to 12 months after recruitment
- Clinical events related to the study conduct that occur after consent but before administration of one of the study vaccines, and which meet the criteria of an SAE

- SAEs considered by the Investigator to be related to one of the study vaccines that occur beyond the defined study period (i.e., more than 12 months after recruitment)

## 10.2 Assessment of Causality

For this study, all local solicited AEs (injection site pain, erythema and induration / swelling) will be considered definitely related to vaccination.

For all solicited systemic AEs, all unsolicited AEs and all SAEs, the Investigator will need to determine whether the particular event is related to study vaccination. All AEs must be recorded in the CRF.

The relationship of the AE to one of the study vaccinations will be specified as follows:

### **Not related**

A clinical event or laboratory test abnormality

- With a time to study vaccine administration that makes a relationship impossible
- That could be explained by concurrent disease or other drugs / chemical (either patho-physiologically or clinically)
- With a time to vaccine administration that makes a relationship improbable (but not impossible)
- That could also be explained by another equally likely cause
- Where concurrent disease or other drugs / chemicals could provide a plausible explanation

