## **2.6 Description of the population to be studied.**

Healthy newborns, greater than 36 completed weeks gestation, will be randomized to receive acellular pertussis vaccine and hepatitis B vaccine at birth (within 120 hours of birth) or hepatitis B vaccine alone.

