### **6.4 Halting Rules**

A DSMB will be established to monitor the safety of the study.

All serious adverse events (SAEs) causally related to the administration of monovalent acellular pertussis vaccine, will be reviewed by the DSMB within 24hrs of notification of the event to the DSMB Chairperson by the Principal Investigator.

The DSMB will make a recommendation regarding continuation of the trial. Enrolment and further dosing of the monovalent acellular pertussis vaccine will be halted pending the outcome of the DSMB review/recommendation.

All other SAEs will be reviewed periodically by the DSMB in accordance with the DSMB Charter.

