### **Related**

A clinical event or laboratory test abnormality

- That occurs in a plausible time relationship to the administration of the vaccines;
- Where the event is definitive pharmacologically or phenomenologically
- That occurs in a reasonable time relationship to the administration of the vaccine
- Where the event is more likely to be explained by the vaccine than any other cause

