## **10.7 Regulatory Requirements**

The sponsors have a legal responsibility to notify the relevant regulatory authorities about the safety of the product under clinical investigation. Prompt notification of SAEs by Investigators is essential so that legal obligations and ethical responsibilities for the safety of other study participants are met.

The Principal Investigator will report all unexpected Serious Adverse Events, causally-related to the monovalent acellular pertussis vaccine, to the Therapeutic Goods Administration (TGA) within 7 days (fatal or life-threatening events) or 15 days (for non-fatal, non-life threatening events).

The Principal Investigator will also report all unexpected or serious adverse reactions causally related to the licensed, concomitant childhood vaccines, to the TGA Office of Medicines Safety Monitoring as soon as possible.

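### The two causality categories in Protocol 10.2 overlap and have no tie rule, so a possibly Pa-related serious event in a newborn can bypass the halt, the 24-hour DSMB review and the expedited TGA report

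*Protocol*

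**What the plan says.** Section 10.2 gives the decision to the site. For solicited systemic events, unsolicited events and SAEs, "the Investigator will need to determine whether the particular event is related to study vaccination". The scale has two levels.

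- *Not related* has five bullets: impossible timing; an event that concurrent disease or other drugs could explain; timing that makes a link improbable though not impossible; an event "That could also be explained by another equally likely cause"; and an event "Where concurrent disease or other drugs / chemicals could provide a plausible explanation".
- *Related* has four bullets: plausible timing; a definitive event in pharmacological or phenomenological terms; reasonable timing; and an event "Where the event is more likely to be explained by the vaccine than any other cause".

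The section does not say whether one bullet is enough or all are needed, or which category wins if both apply.

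Three provisions then depend on the answer. Section 6.4 says that SAEs "causally related to the administration of monovalent acellular pertussis vaccine, will be reviewed by the DSMB within 24hrs of notification", with enrolment and further monovalent Pa dosing halted meanwhile. Section 10.5 has the Principal Investigator notify the DSMB Chair of such SAEs within 24 hours. Section 10.7 states: "The Principal Investigator will report all unexpected Serious Adverse Events, causally-related to the monovalent acellular pertussis vaccine", to the TGA within 7 or 15 days.

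**The concern.** In safety reporting, an event that may or may not be due to the product is normally the one that most needs a quick independent look. Here three of the five *Not related* bullets describe exactly such events, and there is no intermediate level to hold them. A newborn who falls ill soon after the birth visit will often have a competing explanation, and the causal call is made with allocation known (5.4).

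At stake are the speed and consistency of the response. Two sites following the protocol correctly could code the same admission differently. One coding halts enrolment and convenes the DSMB. The other leaves the event for periodic review while newborns continue to be enrolled and dosed. The protocol itself concedes in section 17 that there are few data on responses to DTPa vaccines before 6 weeks of age, so ambiguous early events deserve a clear route.

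**Working it through.** No arithmetic applies: the protocol states no figure on this point, and the finding needs none. The check is to apply the lists to one event and follow the consequences.

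**Step 1. Apply both lists to one event.** Take, as an illustration, a birth-group infant admitted with fever the day after visit 1, where infection and the vaccine seem equally likely.

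| List | Bullets met | Bullets not met |
|---|---|---|
| *Not related* (5) | other disease could explain it; equally likely other cause; plausible alternative | impossible timing; improbable timing |
| *Related* (4) | plausible timing; reasonable timing | definitive event; vaccine more likely than any other cause |

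The event meets three of five bullets on one list and two of four on the other.

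**Step 2. Ask how the bullets combine.** The *Not related* list cannot require all its bullets, because impossible timing and improbable-but-possible timing exclude each other. One bullet must therefore be enough, and the event qualifies as *Not related*. The *Related* list can be read either way:

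- If all four bullets are needed, the event fails, and *Not related* is the only code.
- If one is enough, the event is also *Related*, and nothing says which code prevails.

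So the code is either *Not related* or undetermined.

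**Step 3. Follow the consequences of a *Not related* code.**

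| Route | Section | Needs a causal link to monovalent Pa? |
|---|---|---|
| DSMB review within 24 hours, with halt | 6.4 | Yes |
| Notice to the DSMB Chair within 24 hours, then a meeting | 10.5 | Yes |
| TGA report in 7 or 15 days | 10.7 | Yes, and the event must be unexpected |
| Notice to the Principal Investigator within 24 hours | 10.5 | No |
| Notice to the manufacturer within 24 hours, for monovalent Pa recipients | 10.5 | No |
| Site reports of individual SAEs to ethics committees | 10.5 | No |
| DSMB review of all SAEs; those not causally related, periodically | 10.4.1, 6.4 | No |

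The first three routes are lost and the last four remain. None of the four carries a halt or a stated 24-hour DSMB review.

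**Step 4. Compare what is asked with what is needed.** Section 10.2 introduces the scale with "The relationship of the AE to one of the study vaccinations will be specified as follows", which means any of them. Sections 6.4, 10.5 and 10.7 need attribution to monovalent Pa specifically. Section 2.6 has birth-group infants "randomized to receive acellular pertussis vaccine and hepatitis B vaccine at birth", and the visit 1 row of the schedule (Table 2 in section 8) lists both. An event attributable to either vaccine can be *Related* under 10.2, yet the text does not say whether it is causally related to Pa for the purposes of 6.4.

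**The case against.** The strongest reply is that the safety net does not rest on this classification alone. Every SAE reaches the Principal Investigator within 24 hours. Every SAE in a monovalent Pa recipient reaches the manufacturer within 24 hours whatever its cause. Sites report to ethics committees, and the DSMB reviews all SAEs. This stands, and it limits the finding to delay. It does not remove it, because none of these routes replaces the prompt DSMB review that 6.4 sets up.

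A second reply is that a sensible investigator would code a well-timed event as *Related*. The text allows that, but it equally allows the opposite.

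A third is cost. Section 10.5 requires a DSMB meeting within 24 hours of each notice, and 6.4 ties review to a halt, so a wider definition of related could burden the trial. This is a fair reason to settle those consequences separately from the notification itself.

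Several stronger readings are tempting but unsupported:

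- *That the halt can never fire for such events.* The overlap leaves the code open, and a site may choose *Related*.
- *That the scale misses the very harms the birth dose is most likely to cause.* The protocol gives no expected profile or rate of serious events after birth Pa.
- *That the loss can be sized from an excess over background admissions.* The protocol gives no background rate. A population fraction is also not an individual infant's causal probability, since the investigator has onset time and clinical findings to use.
- *That 6.4 is the only way the trial could be halted.* Section 14.4 rules out only formal statistical stopping rules, and the DSMB Charter is not shown.
- *That blaming hepatitis B vaccine makes the event Not related.* Under 10.2 it could make it *Related*; the gap lies in carrying that answer over to monovalent Pa.

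**Conclusion.** The concern holds as an internal inconsistency with a practical consequence. The two categories are not mutually exclusive and there is no rule for ties. A site that follows the wording can therefore send a possibly Pa-related SAE in a newborn past the halt with 24-hour DSMB review, the notice to the DSMB Chair and the expedited TGA report. The mismatch between any study vaccination in 10.2 and monovalent Pa in 6.4 leaves a second question open for events at the birth visit.

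Its size is a delay, from 24-hour DSMB review to periodic review at an interval the protocol does not state. How many events would be affected cannot be derived from the document. The conclusion rests on the wording alone and assumes that neither the DSMB Charter nor the CRF instructions, which are not shown, already supply a tie rule. This should be fixed; because the causality-independent routes remain, it is not a fatal flaw.

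**What to change.** Reconcile sections 6.4, 10.2, 10.4.1, 10.5 and 10.7, as follows.

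1. In 10.2, move the three uncertain bullets (improbable but possible timing, equally likely other cause, merely plausible alternative) out of *Not related* into a new *Possibly related* level. Narrow the remaining bullet on concurrent disease or other drugs, which would otherwise still capture the same events. State how the bullets combine, so that each event has exactly one code.
2. Count *Possibly related* as related for notice to the DSMB Chair (10.5) and for TGA reporting (10.7).
3. Record causality separately for monovalent Pa. State that another study vaccine given at the same visit is not, by itself, an alternative cause that makes an event unrelated to Pa.
4. Leave it to the sponsor and the DSMB to decide, and write down, whether a possibly related event carries an automatic pause or an immediate meeting.

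The cost is protocol and CRF wording, more expedited notices to the DSMB Chair and some extra DSMB workload. How much depends on the decision in item 4.

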### **Related**

A clinical event or laboratory test abnormality

- That occurs in a plausible time relationship to the administration of the vaccines;
- Where the event is definitive pharmacologically or phenomenologically
- That occurs in a reasonable time relationship to the administration of the vaccine
- Where the event is more likely to be explained by the vaccine than any other cause

## 10.3 Assessment of Intensity

Intensity of solicited AEs will be graded on a four-point scale (none, mild, moderate, severe), as explained in tables 2 and 3 and reported by parents on the diary cards.

Solicited local AEs are defined and should be graded as follows:

**Table 2 Solicited Local AE Definitions and Intensity Grading**

| Injection Site Reaction | Intensity Grading |                                                                           |                                                                     |                                                                                     |
|-------------------------|-------------------|---------------------------------------------------------------------------|---------------------------------------------------------------------|-------------------------------------------------------------------------------------|
|                         | None (0)          | Mild (Grade 1)                                                            | Moderate (Grade 2)                                                  | Severe (Grade 3)                                                                    |
| Pain                    | Absent            | Minor reaction on touch
or
Does not interfere with daily activities | Cries / protests on touch
or
Interferes with daily activities | Cries when limb is moved / spontaneously painful
or
Prevents daily activities |
| Redness (erythema)      | 0                 | ≤ 10 mm                                                                   | > 10 mm to < 30 mm                                                  | ≥ 30 mm                                                                             |
| Induration / swelling   | 0                 | ≤ 10 mm                                                                   | > 10 mm to < 30 mm                                                  | ≥ 30 mm                                                                             |

Solicited systemic AEs are defined and should be graded as follows:

**Table 3 Solicited Systemic AE Definitions and Intensity Grading**

| Symptom                      | Intensity Grading |                                                                                                                               |                                                                                       |                                                                                                |
|------------------------------|-------------------|-------------------------------------------------------------------------------------------------------------------------------|---------------------------------------------------------------------------------------|------------------------------------------------------------------------------------------------|
|                              | None (0)          | Mild (Grade 1)                                                                                                                | Moderate (Grade 2)                                                                    | Severe (Grade 3)                                                                               |
| For all participants  |                   |                                                                                                                               |                                                                                       |                                                                                                |
| Fever (axillary temperature) | < 37.5°C          | ≥ 37.5°C to ≤ 38.5°C                                                                                                          | > 38.5°C to ≤ 39.5°C                                                                  | > 39.5 °C                                                                                      |
| Vomiting                     | None              | Adverse event easily tolerated by the participant, causing minimal discomfort and does not interfere with everyday activities | Adverse event sufficiently discomforting to interfere with normal everyday activities | Adverse event prevents normal everyday activities or requires significant medical intervention |
| Diarrhoea                    | None              | Adverse event easily tolerated by the participant, causing minimal discomfort and does not interfere with everyday activities | Adverse event sufficiently discomforting to interfere with everyday activities        | Adverse event prevents normal everyday activities or requires significant medical intervention |
| Feeding                      | None              | Adverse event easily tolerated by the participant, causing minimal discomfort and does not interfere with everyday activities | Adverse event sufficiently discomforting to interfere with everyday activities        | Adverse event prevents normal everyday activities or requires significant medical intervention |
| Irritability                 | None              | Adverse event easily tolerated by the participant, causing minimal discomfort and does not interfere with everyday activities | Adverse event sufficiently discomforting to interfere with everyday activities        | Adverse event prevents normal everyday activities or requires significant medical intervention |
| Drowsiness                   | None              | Adverse event easily tolerated by the participant, causing minimal discomfort and does not interfere with everyday activities | Adverse event sufficiently discomforting to interfere with everyday activities        | Adverse event prevents normal everyday activities or requires significant medical intervention |
| Restlessness                 | None              | Adverse event easily tolerated by the participant, causing minimal discomfort and does not interfere with everyday activities | Adverse event sufficiently discomforting to interfere with everyday activities        | Adverse event prevents normal everyday activities or requires significant medical intervention |

The intensity / severity of unsolicited AEs will be graded as follows:

**Mild:** Symptoms are easily tolerated and do not interfere with daily activities  
**Moderate:** Enough discomfort to cause some interference with daily activities  
**Severe:** Symptoms that prevent normal, everyday activities

